## Method

### Design

The study is a single-centre, RCT with parallel group design. After a baseline assessment, participants are randomized in a 1:1 fashion, using a computer-generated sequence utilizing permuted blocks of 4, 8 and 10 initiated by the institutional methods centre, to the HHT program or to UC. Since sex and participation in CR can have an impact on the study outcomes, randomization is stratified by patient sex (male/female) and participation in the University of Ottawa Heart Institute (UOHI) CR program (yes/no). The trial began in October 2019 and data collection is ongoing. The protocol was approved by our institutional research ethics board (OHSN-REB# 20190101-01H) and all participants provide informed consent. Figure 1 depicts the study design and cohort flow.

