### Participants

Patients at a large cardiac care hospital in Canada and their partners are approached to participate if they meet the study eligibility criteria, including: (1) being in a romantic relationship of any sexual orientation for at least 1 year; (2) living together for one or more years; (3) the patient having a cardiac event, procedure, or hospitalization in the past 6 months; (4) being 18 years or older; and, (5) being available to participate for 6 months. As a substantial number of participating couples reported high relationship satisfaction and, thereby, likely experience limited benefit from the HHT intervention, in July 2023, another inclusion criterion – one or both partners must score below the satisfied range on relationship quality (i.e., score of <107 on the Dyadic Adjustment Scale (DAS) questionnaire) (Spanier, 1976) - was added as advised by the study biostatistician. Exclusion criteria include: (1) those with any psychiatric or cognitive problems that would impair participation in the HHT program. Staff screen for impairment via chart review. If nothing is documented but a potential participant appears to have these impairments, the study psychologist would determine (either through further chart review or discussion with the research coordinator, referring clinician, or patient) whether participation is appropriate, or (2) planned or active participation in couples’ therapy. Since the HHT program materials were available in English only at the study outset, participants are required to read and understand English. However, the option to complete questionnaires in French or English or speak in their first language during some tasks is possible.

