#### Follow-up assessments

The same procedures are conducted at each follow-up assessment (8 weeks and 6 months). A REDCap link is sent to participants via email or, if preferred, printed questionnaires are sent by post to be completed before the assessment. Patients also report if they enrolled in CR and, if so, in which program options they participated (e.g., exercise, nutrition, stress management class). They also indicate if they partook in any individual or couples-based psychological services. Research staff conducting follow up data collection, intervention infidelity checks, and behavioral coding are blind to the randomized condition. To maximize participant retention, assessments are scheduled to coincide with regular follow-up appointments or rehabilitation sessions at the UOHI whenever possible. Appointment reminders and parking passes are provided at each assessment, and gift cards are distributed after their final assessment. Efforts are made to collect primary outcome data despite potential deviation from study protocols. For example, the completion of online questionnaires will still be offered to those who might withdraw from in-person study activities.

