#### Planned statistical analyses

SPSS and HLM statistical software will be used to analyze the study data. Demographic and clinical variables reported by participants who complete assessments will be compared to those lost to follow-up to verify the representativeness of the cohort. Analyses will be with the intent to treat sample. Research staff record all cases of missing data, including non-retention of participants or withdrawal of consent. Where data are missing, the frequency and reasons for missing data will be recorded. Missing data will be statistically examined for patterns of systematic missingness, and an appropriate missing data strategy will be employed. In situations where data are missing, the data collected up to that point will be used, provided the participant has not withdrawn their consent or requested that the information be removed. For the *primary outcome*, a multilevel analysis of covariance with individuals’ DAS values at 8 weeks as the dependent variable and DAS baseline scores as the covariate at level 1 of the model. The study conditions (HHT vs. UC) to which couples were assigned will be dummy-coded and entered at level 2. To evaluate *secondary outcomes,* a three-level multi-level model for repeated measurements will be utilized. The analysis will include repeated measurements within individuals in Level 1, between-individual variability in Level 2, and couples in Level 3. Within-couple slope variances will be fixed at Level 2 but allowed to vary at Level 3 (Atkins, 2005). A linear parameter will model changes in outcomes from baseline to 8 weeks to 24 weeks. The study condition (HHT vs. UC) will be dummy-coded and modeled as a fixed effect at Level 3. Baseline patient control variables will be entered at Level 2. Binary outcomes will be modeled utilizing a logit link. Improved model fit between nested models will be evaluated using deviance statistics and a chi-square distribution. Effect sizes will be assessed with the pseudo-R squared statistic or Cohen’s d when appropriate. Full maximum likelihood estimation method will be applied for all analyses. For both primary and secondary analyses, we will also conduct stratified analyses for all outcomes by sex (male/female), CR participation (yes/no), and relationship quality (distressed/not distressed on the DAS).

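### Subgroups are to be examined only by separate stratified analyses, which do not test whether the HHT effect differs, and DAS distress is not defined per person or per couple

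*Protocol article*

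**What the plan says.** Under Planned statistical analyses, the protocol article adds to the main models that "we will also conduct stratified analyses for all outcomes by sex (male/female), CR participation (yes/no), and relationship quality". The third factor is given as "relationship quality (distressed/not distressed on the DAS". This covers both the primary and the secondary analyses, and no term for condition by factor is named.

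The same section takes "individuals’ DAS values at 8 weeks as the dependent variable", so the primary model works on persons nested in couples. Condition is a couple-level variable: the arms "to which couples were assigned will be dummy-coded and entered at level 2".

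Two other sections bear on how strata can be formed. Under Design, "randomization is stratified by patient sex (male/female" and by participation in the hospital's cardiac rehabilitation (CR) program; baseline DAS is not a randomisation stratum. Under Participants, the criterion added in July 2023 is that "one or both partners must score below the satisfied range on relationship quality", meaning a DAS score below 107. The reason given is: "As a substantial number of participating couples reported high relationship satisfaction and, thereby, likely experience limited benefit from the HHT intervention".

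**The concern.** A stratified analysis asks, within each stratum, whether HHT differs from usual care. Whether the effect of HHT differs between strata is a separate question, and only a contrast of the two stratum effects answers it. When one stratum reaches significance and the other does not, the pair of results invites the reading that HHT works in one group only. That pattern is common even when the effect is identical in both.

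The question has weight here because the article itself expects couples who are already satisfied to gain little. Variation of the effect with baseline DAS is therefore something readers will look for.

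The unit of the distress stratum is a second matter. With individual scores as outcome and eligibility open to couples with one partner below 107, classing persons and classing couples give different strata and possibly different answers. The article does not say which is meant.

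**Working it through.** **Inputs.** From Sample-size calculation: difference 3.9, SD of change 10, 210 couples allocated 1:1 (105 per arm), alpha 0.05, power 80%. Sidedness is not stated; two-sided is assumed because it reproduces the plan's figure, whereas one-sided would need 164 couples. Stratum sizes are not given, so the splits below are assumptions. As in the plan's own 210-couple figure, each couple contributes one value and clustering by therapy group is ignored.

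**The plan's figure.** The t-test sample size for a standardised difference of 0.39 is 104.2 per arm, rounded up to 105, giving 210 couples. With 105 per arm, SE = 10 × √(2/105) = 1.380 and 3.9/1.380 = 2.826, so power = Φ(2.826 − 1.960) = 0.807 (0.803 with the t-test). The stated 80% reproduces.

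**One of two equal halves, same true effect of 3.9 in both.** Each half has 52.5 couples per arm. SE = 10 × √(2/52.5) = 1.952 and 3.9/1.952 = 1.998, so power = Φ(0.038) = 0.515. The strata share no couples, so P(exactly one significant) = pA(1 − pB) + pB(1 − pA) = 2 × 0.515 × 0.485 = 0.50.

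| Assumed split of 210 couples | Couples per arm | Power in each stratum | Exactly one significant |
|---|---|---|---|
| 50/50 | 52.5 and 52.5 | 0.515 and 0.515 | 0.50 |
| 60/40 | 63 and 42 | 0.591 and 0.431 | 0.51 |
| 70/30 | 73.5 and 31.5 | 0.657 and 0.340 | 0.55 |
| 80/20 | 84 and 21 | 0.715 and 0.243 | 0.61 |

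With 304 couples analysed, the last column runs from 0.44 (50/50) to 0.62 (80/20).

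**Three factors together.** A simulation used 20,000 trials of 210 couples, one score per couple and three independent factors split 50/50. With a uniform 3.9-point effect, at least one of the three factors showed significance in one stratum only in about 75% of trials. An interaction test gave a false signal in about 5% per factor and about 15% for any of the three.

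**Price of the interaction test.** For equal halves, the SE of the difference between stratum effects is 10 × √(2/52.5 + 2/52.5) = 2.760. Power to detect a true 3.9-point difference between strata is Φ(3.9/2.760 − 1.960) = Φ(−0.547) ≈ 0.29, and the 95% CI half-width is 1.96 × 2.760 = 5.4 points. With 304 couples (76 per arm per half), SE = 10 × √(4/76) = 2.294, power is about 0.40 and the half-width is 4.5 points.

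**Unit of the distress stratum.** The documents give no joint distribution of partners' scores. Assuming SD 17, a mean of 100 to 112 and a between-partner correlation of 0.3 to 0.7, about 30% to 67% of couples with at least one partner below 107 have exactly one partner below it. Classing by person would place these couples in both strata, so the choice of unit is material.

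**The case against.** This is a condensed article and the analysis plan is not shown. Interaction terms, subgroup definitions and an exploratory label often sit there. The article also plans to compare nested models by deviance, a framework that could carry an interaction test. All this stands as far as omission goes: interaction tests are not excluded. The point is confined to what the article does commit to, which is stratified analysis of every outcome.

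Four stronger readings are tempting, and the documents support none of them.

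- A reader might infer that effect modification will be decided by comparing stratum p-values. The article does not say so, and the stated objectives contain no subgroup aim. The 50% figure describes what happens if the strata are read that way.
- A reader might infer that CR strata will use enrolment after randomisation, because at follow-up "Patients also report if they enrolled in CR and, if so, in which program options they participated". Nothing ties that item to the strata. Sex and CR appear with the same levels as in the randomisation, so the natural reading is the couple-level, pre-randomisation factors.
- A reader might infer that splitting couples would bias the results. It would not: condition is assigned by couple, so HHT against usual care within a stratum remains a randomised comparison. Moreover, if sex were taken per person, each opposite-sex couple would give one member to each stratum. Each stratum would then keep about 105 persons per arm and about 80% power, and discordance would be at most about 2 × 0.80 × 0.20 = 32%. The 50% figure therefore applies to couple-level strata only.
- A reader might infer that the July 2023 eligibility change will be justified from these analyses. Nothing says so.

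Low interaction power is a fair objection to expecting much from the alternative. It does not rescue separate strata, which face the same lack of information without showing it.

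**Conclusion.** The point holds in a limited form. The only subgroup method named does not test whether the effect differs. Under a uniform 3.9-point effect, significance in exactly one stratum would occur in about 50% of trials for equal halves of 210 couples, and in about 51% to 61% for splits from 60/40 to 80/20. These figures rest on the plan's difference and SD, two-sided 5% tests, couple-level strata and assumed stratum sizes. In addition, the unit for distress is open where it matters, because couples with only one partner below 107 are eligible. The randomised primary comparison is not affected.

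**What to change.** For each outcome, fit the full-sample multilevel model with condition-by-factor interactions. Report the stratum effects from that model together with the interaction estimate and its CI. Use couple-level factors fixed before randomisation:

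- patient sex and CR participation, as used in the randomisation;
- a couple-level baseline DAS, such as the lower of the two partners' scores, which matches the eligibility rule and is preferably kept continuous.

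Label these analyses exploratory and treat those of the secondary outcomes as descriptive.

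The cost is wording: the data are the same and data collection is still under way. The drawback is precision. With about 29% power at 210 couples and 40% at 304 for a 3.9-point difference between equal strata, and less for unequal ones, the intervals will be wide. The report should say that a non-significant interaction does not show equal effects. Couples in which both partners score 107 or more can come only from recruitment before July 2023, so a comparison across that boundary is tied to recruitment period, and this should be stated as well.

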### Anticipated outcomes

It is expected that participants randomized to HHT intervention will report higher RQ (≥3.9 points on the DAS) and improved secondary outcomes as compared to those in UC.

### Dissemination plans

Trial results will be shared through published manuscripts to participants, healthcare professionals, and the public. To enhance the accessibility of the research findings, results will also be disseminated in interactive formats. For example, findings will be presented during hospital rounds and in-services to inform clinical staff of the importance of relationship quality and encourage the inclusion of the partner in the care team. Results will be disseminated to research participants and the lay public in formats such as community presentations, in-person research dissemination events, and media releases.

## Discussion

To our knowledge, the HHT randomized trial is one of few studies evaluating a relationship-enhancement intervention specifically designed for couples facing the challenges of CVD. The HHT intervention is rooted in an evidence-based theoretical framework, expert recommendations (Johnson, 2004; Johnson, 2008), and direct input from couples managing CVD (Tulloch et al., 2020). Further, the intervention and trial design address many methodological limitations in the couples-based literature in the cardiac domain, including small sample sizes; samples restricted to specific cardiac populations limiting generalizability; data collection limited to patients only; limited and solely subjective measures of RQ, and, few relevant and cardiac-specific health outcomes. Indeed, the current trial has several strengths, including the RCT design, comprehensive assessments using validated, objective and self-report measures, partner-specific data collection, and aims to recruit a large sample. Our proof-of-concept data showed pre-post improvements in RQ, mental health and quality of life (Tulloch et al., 2021). The present RCT now tests if the HHT intervention is better than usual care on many relationship and health outcomes. With significant findings, the finalized intervention will signal if effectiveness testing is required and may indicate that the intervention should be systematically implemented at other cardiac care sites, as well as pave the way for future intervention research for other chronic conditions (e.g., cancer). If positive, this research may also contribute to a shift from medical and physical indicators alone to a more holistic approach which comprises the promotion of enhanced social support through improved couple relationships, thereby enhancing cardiovascular outcomes. Considering that partners often share similar age and lifestyle factors as patients, they too may be vulnerable to poor mental or physical health outcomes, and programs such as HHT enhancing RQ may improve partners’ health along with improving the CVD recovery process for patients (Bouchard et al., 2019).

